## Materials and methods

### Study setting and participant recruitment

Study participants will be recruited nationwide, targeting individuals with lived experience of EDs, GPs, and medical students. Recruitment will be conducted through offline and online methods, including leaflets, personal recommendations and mass emailings. We will perform extensive web-scraping of contact registers of medical professional organizations and apply for access to the federal register of physicians for a nation-wide probability sample of GPs. Medical students in their clinical training year will be recruited through local university networks and mass emailing via clinical training year coordinators at medical faculties across all German universities.

Individuals with lived experience will be rewarded 100 € for participating in the focus group, and 75 € for each attended advisory board meeting (for further details, see section on Patient and Public Involvement). GPs participating in the online training will receive 25 € reimbursement upon completion as well as 1 continuing medical education (CME) credit point, and another 50 € for participating in the telephone-based qualitative interview. Medical students will be eligible to register for a prize draw to win online vouchers worth 375 € in total. All participants will receive a certificate upon successful completion of the online training.

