### Participant timeline

Individuals interested in taking part in the study can self-enroll via a webform on the project website (https://maennermitessstoerung.rub.de), which is referenced as link and QR code in leaflets and mailings. At enrollment (-t_1_), participants will answer baseline and sociodemographic questions, undergo eligibility assessment and be allocated to their respective participant group (GP or medical student) and study arm (intervention or wait-list control). Participants allocated to the wait-list control groups will be informed that they need to wait 14 days for the online training. Participants of the wait-list control groups will be meanwhile invited to a quantitative pre-participation assessment at t_1_ within the two-week waiting period, after which they will receive the personalized login credentials for the online learning platform to administer a quantitative pre-intervention assessment at t_2_ (end of the waiting period), then followed by the actual online training and a quantitative post-intervention assessment at t_3_. By contrast, participants allocated to the intervention group directly receive personalized login credentials for the learning platform at t_1_ (enrollment) and administer pre-intervention assessments before participating in the online training, followed by a quantitative post-intervention assessment at t_2_. Intervention group participants will be contacted to administer a quantitative post-participation/follow-up assessment at t_3_ another 14 days after they have completed the online training. Both groups will have 14 days to complete the training. To minimize the risk of participant dropout, participants will receive reminder emails on several time points during their participation (a reminder for completing the pre-survey 1 week after receiving the pre-survey link, a reminder for completing the online training one week after receiving login credentials and another reminder two days before termination of the 14-days participation time window, and a reminder for the post-survey 1 week after receiving the post-survey link). This procedure applies to both GPs and medical students allocated to the respective study arms. Finally, selected participants of the GP groups are invited to a qualitative telephone interview (t_4_) about four months after completion of the online training and respective quantitative assessments (see Fig 2).

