### Data analysis

Qualitative data analyses will be conducted using MAXQDA [39] version 24.5.1. Quantitative data analyses will be performed using R [40] and SPSS [41].

Regarding quantitative data, we will conduct two sets of analyses. These will be per-protocol analyses and intention-to-treat analyses. For the per-protocol analyses, we will compute a 2 (intervention vs. wait-list control) x 3 (timepoint) mixed-measures ANOVA per each outcome and participant group, accounting for the two groups (intervention vs. wait-list control group) and the three time points of quantitative assessment. The intention-to-treat analyses will be conducted using a corresponding 2 x 3 mixed model, with by-participant random intercepts (and slopes, if justified by the data). We will also conduct contrast analysis for the 2 x 3 design (1 −1 −1 1 1–1) to directly test the predicted interaction pattern. The change from pre- to post-intervention will be estimated with a paired-samples t-test for any participant that completed the intervention. Quantitative implementation data will be aggregated descriptively and compared between groups.

The per-protocol analysis will use case-wise exclusions in case of missing data. In case of dropout/case exclusions, the ITT mixed model will be conducted with and without multiple imputation based on predictive mean matching functioning as a sensitivity analysis.

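### Intervention-arm t3 is dated from finishing the course and t2 has no calendar day, so the intention-to-treat model may credit non-completers with completers' gains, and its imputation check cannot show it

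*Protocol article*

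**What the plan says.** All the timing rules are in the protocol article, under Participant timeline.

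- **Intervention arm, t2:** participants "administer pre-intervention assessments before participating in the online training, followed by a quantitative post-intervention assessment at t_2". This gives an order of events and no day.
- **Intervention arm, t3:** due "another 14 days after they have completed the online training". The clock starts at the participant's own completion.
- **Wait-list arm, t2:** participants receive platform access "to administer a quantitative pre-intervention assessment at t_2_ (end of the waiting period"). This is a fixed point, before any training.
- **Access window:** "Both groups will have 14 days to complete the training".
- **Reminders:** the list includes "a reminder for the post-survey 1 week after receiving the post-survey link", without saying who is sent that link or when.

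Under Data analysis, the intention-to-treat analysis is a 2 x 3 mixed model with random participant effects. For dropout or exclusions, "the ITT mixed model will be conducted with and without multiple imputation based on predictive mean matching functioning as a sensitivity analysis". Under Study setting and participant recruitment, "GPs participating in the online training will receive 25 € reimbursement upon completion".

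**The concern.** The randomised comparison sits at t2, because by t3 the wait-list arm has also been offered the course. At t2 one arm's assessment follows the training and the other's follows the calendar. Someone in the intervention arm who abandons the course reaches no stated trigger for t3 and only a loosely defined one for t2. A wait-list participant needs no training to reach t2. Missing data at t2 can therefore depend on adherence in one arm and not in the other.

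Payment on completion pushes the same way. A wait-list participant at t2 can still earn it, whereas an intervention participant who has given up the course appears to have lost that reason to answer.

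The article already plans a per-protocol analysis. The intention-to-treat analysis adds information only if it represents everyone randomised. If those observed are essentially those who finished, it repeats the completer result under another name and overstates the effect of offering the course.

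**Working it through.** **The plan's own figure.** Inputs from Sample size: f = 0.15, r = 0.50, 2 groups, 3 time points, alpha 0.05, power 0.80, epsilon 1. The noncentrality is f² x N x m / (1 - r) = 0.0225 x 74 x 3 / 0.5 = 9.99, with 2 and (74 - 2) x 2 = 144 degrees of freedom. Power is 0.806 at N = 74 and 0.795 at N = 72, so the stated 74 reproduces. The point does not affect it.

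**Implied loss allowance.** About 100 GPs are sought for 74 needed: 1 - 74/100 = 26%. The article states no rate. This allowance spans both arms and also covers poor-quality data.

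**Size of the bias.** Let p be the share of the intervention arm that does not complete and is unmeasured at t2, D the completers' gain, and q the fraction of D that non-completers actually gain.

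- Effect of offering the course: D x [1 - p(1 - q)].
- A missing-at-random analysis with no data from non-completers returns about D.
- Relative overstatement: 1/[1 - p(1 - q)] - 1, which does not depend on D.

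| p | q = 0 | q = 0.5 |
|---|---|---|
| 10% | 1/0.90 - 1 = 11% | 1/0.95 - 1 = 5% |
| 26% | 1/0.74 - 1 = 35% | 1/0.87 - 1 = 15% |
| 40% | 1/0.60 - 1 = 67% | 1/0.80 - 1 = 25% |

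**Simulation of the planned model.** The setting was 50 per arm, unit SD, r = 0.5 and 120 to 150 runs per row. These assumptions are not in the article: completers gain 0.5 SD, non-completers gain nothing, non-completion is unrelated to baseline, intervention non-completers are missing at t2 and t3, and wait-list non-completers are missing at t3. The mixed model had random intercepts. Predictive mean matching was done within arm from the t1 score, and the difference in t1-to-t2 change was then taken.

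| p | True effect at t2 | Mixed model, non-completers missing | Predictive mean matching | Mixed model, all measured |
|---|---|---|---|---|
| 10% | 0.45 | 0.48 | 0.49 | 0.43 |
| 20% | 0.40 | 0.49 | 0.49 | 0.39 |
| 26% | 0.37 | 0.49 | 0.49 | 0.36 |
| 40% | 0.30 | 0.49 | 0.48 | 0.29 |

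The Monte Carlo standard error of the mixed-model estimate is about 0.02. With non-completers missing, both planned analyses stay near the completers' 0.5 SD whatever the true effect, and they agree with each other. With everyone measured, the same model follows the true effect. At p = 26%, the share of significant t2 contrasts is 0.62 with non-completers missing and 0.50 with all measured.

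The simulation builds in total missingness and zero gain. It shows how the planned analyses behave under that premise and is not evidence for the premise.

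**The case against.** A reader might infer that non-completers are unmeasured by design. The article does not say so. The words about completion govern t3 only; for t2 the text gives a sequence, and dependence on finishing is an inference. Nothing withholds a survey from anyone. There is a separate post-survey link with its own reminder, and its recipients and send date may be settled in the full protocol or in the schedule figure, which is not shown.

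The wait-list t2 is also not assured: it is reached through platform credentials, so people who never log in may be missing there too. Under Data collection methods, compensation is tied to the survey as well as the course, so the payment rule does not show that non-completers are shut out. All of this stands. It weakens the claim about t2 from certain to likely.

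A reader might also take 35% as the expected bias. The article does not support that. It assigns the whole implied allowance to intervention-arm non-completion and assumes no gain from partial use of a six-module course.

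Finally, a missing-at-random mixed model with multiple imputation is conventional, and imputation detail is commonly left to an analysis plan. That is fair for the detail. But the article itself names the sensitivity analysis, and the one it names shares the assumption of the model it is meant to check.

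**Conclusion.** The point holds in conditional form. As written, t3 in the intervention arm is undefined for anyone who does not complete. Missingness at t2 is likely to depend on adherence more in that arm than in the wait-list arm, because only the wait-list t2 is fixed in time and independent of training. To the extent that non-completers are unmeasured, the intention-to-treat label is not earned, and agreement between the model with and without imputation says nothing about whether the data are missing at random.

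The direction of bias is towards overstating the effect, provided non-completers gain less than completers. Its size depends on a non-completion rate and a partial gain that the article does not give. It disappears if everyone is surveyed regardless of progress.

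**What to change.** **Schedule.** State that t2 and t3 surveys go to every randomised participant whatever their training progress, on calendar-anchored dates:

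- intervention t2 no later than the end of the 14-day access window, and t3 14 days after that;
- wait-list t2 as now, and t3 no later than the end of that arm's access window.

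**Analysis.** For participants enrolled before the change, and for any data still missing, keep the missing-at-random analyses. Beside them, add one in which intervention-arm non-completers are imputed from the wait-list t1-to-t2 change, with a delta tipping point. Report completion and t2 response by arm.

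**Cost.** A few more survey emails, a changed link trigger and some extra analysis code. Under Recruitment, data collection began in July 2024, so the schedule change may reach only later participants. It would put two survey timings in one trial, which must be documented as a deviation. The analysis change remains possible whatever the stage of recruitment. If the full protocol already sends the surveys to everyone, the schedule part needs only a clarifying sentence.

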**Fig 2 pone.0333997.g002:**
[figure not shown]
Schedule of participant acquisition, enrolment, interventions and assessments. CME = Continuing Medical Education; OMS-HC = Opening Minds Stigma Scale for Health Care Providers; GSE = General Self-Efficacy Scale; WEM = Scale on the Perception of Eating Disorders in Men; TMF = Traditional Masculinity-Femininity Scale; GP = General practitioner; ED = Eating disorder; ^1^ in intervention group; ^2^ in wait-list control group; crosses in brackets indicate optional assessments.

### Sample size

To determine the appropriate sample size for the planned quantitative analysis (e.g., a 2x3 repeated measures ANOVA with a within-between interaction), an a priori power analysis was conducted using G*Power 3.1.9.7 software [30]. The aim was to achieve a power of.80 [31] with an alpha level of.05. A small-to-medium effect size (*f* = 0.15) as found in prior ED-related anti stigma research [15] and moderate correlation (*r* = .50) among the repeated measures were assumed, as observed in similar fields and due to practical significance considerations. The epsilon (ε) was set to 1, assuming sphericity, which is the most conservative scenario. Using these parameters, the G*Power analysis indicated that a total sample size of 74 participants is required, i.e., a minimum of 37 participants per group. Considering dropouts and cases with insufficient plausibility or quality of data, the study aims for an experimental group of approximately 50 GPs and a wait-list control group with further 50 GPs. To estimate the needs and benefits of future curricular use, the intervention will also be made accessible to approximately 50 medical students in their clinical training year. For the qualitative analyses, up to ten participants with lived experience of EDs and additional GPs for the pre-implementation focus group and panel discussion, and up to 50 GPs for the telephone-based qualitative post-implementation interviews were considered sufficient.

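### The f = 0.15 behind the sample size means an arm difference of about 0.64 SD at t2, and no planned test isolates that randomised comparison

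*Protocol article*

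**What the plan says.** **Sample size.** The calculation is for "a 2x3 repeated measures ANOVA with a within-between interaction". The effect entered is described as "A small-to-medium effect size (*f* = 0.15) as found in prior ED-related anti stigma research [15". Dependence within participants is covered by a "moderate correlation (*r* = .50) among the repeated measures were assumed". For the error rates the article writes "The aim was to achieve a power of.80 [31] with an alpha level of.05", and for the covariance structure "The epsilon (ε) was set to 1, assuming sphericity". The result is "a total sample size of 74 participants is required, i.e., a minimum of 37 participants per group". To allow for dropout and unusable data, "the study aims for an experimental group of approximately 50 GPs and a wait-list control group with further 50 GPs".

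**Data analysis.** For the per-protocol set, "we will compute a 2 (intervention vs. wait-list control) x 3 (timepoint) mixed-measures ANOVA per each outcome and participant group". A corresponding 2 x 3 mixed model serves the intention-to-treat set. A focused contrast is added with weights 1, −1, −1 for one arm and 1, 1, −1 for the other (read in the order arm, then time), and is described as a direct test of the predicted interaction. A paired t-test estimates pre-to-post change in everyone who completes the training.

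**Participant timeline.** At t2 the intervention arm has been trained and the wait-list arm has not. At t3 the wait-list arm is measured just after its training and the intervention arm at a follow-up 14 days after completing its own.

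**The concern.** Randomisation gives one comparison of trained with untrained participants: the arms at t2. At t3 both are trained, so an arm difference there compares follow-up with immediate post-test.

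Two things follow. First, the sample size is expressed as an interaction f, which depends on the whole pattern of six cell means. A reader cannot tell from it what difference at t2 the trial can detect, and may take the label to describe the gap between arms. Second, the efficacy tests listed do not single out the t2 comparison, so a significant result need not show benefit of training over no training.

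**Working it through.** **1. Reproduce the plan's N.** Inputs from Sample size: f = 0.15, r = 0.50, ε = 1, α = 0.05, power 0.80, 2 arms, 3 time points. In the default G*Power convention λ = 3N·f²/(1 − r) = 6N·f², with df1 = 2 and df2 = 2(N − 2).

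- N = 74: λ = 6 × 74 × 0.0225 = 9.99, df 2 and 144, power .806.
- N = 72: power .795.

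So 74 is the smallest total with equal arms, as stated. The partial-eta-squared convention would give 218. This settles which f is meant: the SD of the interaction effects divided by the within-cell SD.

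**2. Convert f to a difference at t2.** The contrast weights imply, up to sign, means (0, d, d) for intervention and (0, 0, d) for wait-list. Removing the arm and time effects leaves residuals −d/6, +d/3, −d/6 in the intervention arm and the opposite signs in the other. Their mean square is

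(4·d²/36 + 2·d²/9)/6 = (d²/3)/6 = d²/18,

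so f = d/√18 and d = 0.15 × 4.243 = **0.636 SD**. A simulation of 20,000 trials at 37 per arm gave power .809 at this d.

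**3. How far this depends on the pattern.**

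| Means, intervention / wait-list | f/d | d at t2 when f = 0.15 |
|---|---|---|
| (0, d, d) / (0, 0, d), as predicted | 0.236 | 0.64 |
| (0, d, d/2) / (0, 0, d), half fading | 0.312 | 0.48 |
| (0, d, d) / (0, 0, d/2), half catch-up | 0.204 | 0.73 |
| (0, d, d) / (0, 0, 0), controls never trained | 0.236 | 0.64 |
| (0, d) / (0, 0), t1 and t2 only | 0.250 | 0.60 |

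The last two rows show that neither t3 nor the second degree of freedom creates the size. A 1-df t1–t2 interaction at f = 0.15 still means 0.60 SD and needs N = 90. The size comes from converting an interaction f to a mean difference.

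**4. Do the planned tests isolate t2?**

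- *Omnibus F.* Means (0, 0, 0) and (0, 0, d), with no difference at t2, also give f = d/√18. The test is equally sensitive to a difference at t3 alone.
- *Contrast.* Summed over arms, the weights are 2, 0, −2. If both arms have the same means (a, b, c), the contrast equals 2a − 2c, which is non-zero whenever t1 and t3 differ, even with no arm difference at any time.
- *Paired t-test.* It has no control comparison.

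**5. The t2 difference adjusted for t1.** With n per arm and r = 0.50, SE = √(2(1 − r²)/n) = √(1.5/n) SD: 0.201 at n = 37 and 0.173 at n = 50. Power is from the noncentral t with noncentrality d/SE; for the ANOVA it is from λ = 6N·d²/18.

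| | ANOVA, 37/arm | Adjusted t2, 37/arm | ANOVA, 50/arm | Adjusted t2, 50/arm |
|---|---|---|---|---|
| Power at d = 0.636 | .81 | .88 | .91 | .95 |
| Power at d = 0.30 | .24 | .31 | .32 | .40 |
| d detectable with 80% power | 0.63 | 0.57 | 0.54 | 0.49 |

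The gain comes from baseline adjustment. A simple t1–t2 change score at 37 per arm has power .77 at d = 0.636, below the ANOVA's .81.

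**The case against.** The sample-size arithmetic is right, and small-to-medium is a fair label on the conventional f scale (0.10 small, 0.25 medium). The protocol never claims a standardised mean difference. At the effect it assumes, power is .81 with 74 participants and .91 if all 100 GPs are retained. A focused contrast and a mixed model are also planned, the ANOVA is introduced only as an example, and ANCOVA against repeated-measures ANOVA is partly a choice between valid methods. All of this stands, except that the contrast as weighted does not do the job given to it.

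Two stronger readings are tempting, and the documents support neither.

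- *That the trial is badly underpowered for its own assumption.* This follows only if 0.15 is read as a two-group f, so that d = 2 × 0.15 = 0.30. The reproduced N shows that the calculation used the interaction f. What the cited study reported, and on which scale, cannot be checked from the article. The power of .24 or .32 at 0.30 SD therefore describes an effect the plan did not assume, and adjustment would not rescue it.
- *That including t3, or spending a second degree of freedom, inflates the detectable difference.* The pattern table above rules this out.

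**Conclusion.** The concern holds in two limited parts. First, the article leaves its effect size untranslated: under its own predicted pattern, f = 0.15 is about 0.64 SD between arms at t2. This assumes full catch-up by the wait-list arm, no fading in the intervention arm, r = 0.50 and equal variances. Half fading or half catch-up moves the figure to 0.48 or 0.73 SD. On the usual conventions for a mean difference (0.5 medium, 0.8 large), 0.64 is not small-to-medium, although the f label itself is not an error.

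Second, no test described isolates the only randomised trained-versus-untrained comparison. The omnibus F can respond to t3 alone, the contrast absorbs change common to both arms, and the paired test is uncontrolled. This matters more for interpretation than for power. The power gain from the better test is real but modest, 0.05 to 0.06 SD in detectable difference.

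**What to change.** 1. Name the between-arm difference at t2, adjusted for the t1 value, as the main efficacy test for each outcome. This can be an ANCOVA or the equivalent contrast from the mixed model already planned.
2. Keep the 2 x 3 ANOVA as secondary and describe t3 as durability only. If the focused contrast is kept, do not present it as a pure interaction test with its current weights.
3. Add to Sample size the difference at t2 detectable with 80% power, like for like: 0.63 SD (ANOVA) and 0.57 SD (adjusted t2) at 37 per arm; 0.54 and 0.49 SD at 50 per arm. State the assumed pattern, and say that a difference near 0.30 SD would probably be missed with either test.

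The cost is wording and one documented deviation. Both measurements are already collected and no participants are added. Because the trial was preregistered and recruitment began in July 2024, the change should be fixed before outcomes are compared by arm and reported as the Protocol amendments section requires.

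### Setting ε = 1 is the most favourable sphericity assumption, not the most conservative one, so the stated 74 is a minimum rather than a cautious figure

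*Protocol article*

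**What the plan says.** The Sample size section of the protocol article bases its calculation on "a 2x3 repeated measures ANOVA with a within-between interaction" and reports that "an a priori power analysis was conducted using G*Power 3.1.9.7 software". The targets are "a power of.80 [31] with an alpha level of.05". The effect size is f = 0.15, and a "moderate correlation (*r* = .50) among the repeated measures were assumed". On sphericity it says: "The epsilon (ε) was set to 1, assuming sphericity, which is the most conservative scenario". The result is that "a total sample size of 74 participants is required, i.e., a minimum of 37 participants per group".

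The section then raises the target to about 50 GPs per arm, 100 in all, to allow for dropout and unusable data. It gives no dropout rate and no power at any other value of ε.

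The Data analysis section names the 2×3 mixed ANOVA as the per-protocol analysis for each outcome and participant group, with case-wise exclusion of missing data. It also plans a linear mixed model for the intention-to-treat analysis and a single contrast for the predicted interaction pattern.

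**The concern.** In a sample-size calculation, a conservative input is one that pushes the required N up. ε measures departure from sphericity. It equals 1 when sphericity holds and can fall to 1/(m − 1), which is 0.5 for m = 3 time points. The Greenhouse–Geisser type of correction reduces the degrees of freedom as ε falls, and G*Power also scales the noncentrality by ε. Under that method ε = 1 is the setting with the smallest required N.

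The section therefore presents a best case as a worst case. A reader would conclude that 74 analysable GPs guarantee at least .80 power whatever the covariance structure. Someone interpreting a null interaction in the per-protocol ANOVA could overrate the power behind it.

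**Working it through.** **Inputs** (all from Sample size): k = 2 groups, m = 3 time points, f = 0.15, r = .50, α = .05, target power .80, equal groups.

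**Formulas** (G*Power, repeated measures, within-between interaction):
- λ = f² · N · m · ε / (1 − r)
- df1 = (k − 1)(m − 1)ε = 2ε
- df2 = (N − k)(m − 1)ε = 2(N − 2)ε
- power = P(F′ > critical F), where F′ is noncentral F with df1, df2 and λ

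**Reproducing the plan's figure (ε = 1).**
- N = 74: λ = 0.0225 × 74 × 3 / 0.5 = 9.99, df = 2 and 144, power .806.
- N = 72: λ = 9.72, df = 2 and 140, power .795.

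The smallest even N reaching .80 is 74, which matches the protocol exactly.

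**Lowering ε with everything else fixed.** For N = 74:
- ε = 0.75: λ = 9.99 × 0.75 = 7.49, df = 1.5 and 108, power .719.
- ε = 0.5: λ = 9.99 × 0.5 = 5.00, df = 1 and 72, power .597.

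| ε | Power, N = 74 | Power, N = 100 (no loss) | Required N |
|---|---|---|---|
| 1.0 | .806 | .914 | 74 |
| 0.9 | .775 | .891 | 80 |
| 0.75 | .719 | .846 | 90 |
| 0.6 | .650 | .784 | 106 |
| 0.5 | .597 | .730 | 120 |

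Power falls and required N rises at every step below ε = 1.

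**Smallest ε that still gives .80, by number analysed:**
- 74 analysed: about 0.98
- 80: about 0.87
- 85: about 0.80
- 90: about 0.74
- 100: about 0.635

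Going from 100 to 74 is a 26% loss. At that loss almost no tolerance for non-sphericity remains; at smaller losses some does.

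**How far the ε scaling can be trusted.** Scaling λ by ε is an approximation. A limited simulation of the Greenhouse–Geisser-corrected test (4,000 replicates, f = 0.15, arm difference at t2 only, unit variances, average correlation .50) gave mixed results:
- Three covariance patterns with ε of about 0.86 kept power between about .81 and .85 at N = 74, so there was no loss.
- A pattern with t1 and t3 correlated at .8 and the other pairs at .35 (ε of about 0.74) gave about .7 at N = 74 and .82 at N = 100.

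The covariance patterns are assumptions, because the protocol gives no correlation matrix. Depending on where the effect sits relative to the correlations, actual power can lie above or below the table.

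**The case against.** The best reply is that only the wording is wrong and that the design already covers most of the consequence. Much of this stands.

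- **The target is 100, not 74.** A reader might infer that neither number secures .80 once ε is below 1. For 100 that is not supported: with no loss it holds .80 over most of the possible range and fails only below about 0.635.
- **The margin from 74 to 100.** A reader might infer that a margin meant for dropout cannot absorb any non-sphericity. No dropout rate is stated, and any loss below 26% leaves room. The margin does shrink as losses grow, because the per-protocol ANOVA drops incomplete cases.
- **The staggered design.** A reader might infer that sphericity must fail because the arms receive training at different times. That describes the means; sphericity concerns the covariance of the repeated measures. The variable assessment spacing in Participant timeline makes unequal correlations possible, but the protocol gives nothing from which to size this.
- **How low ε could be.** The 0.5 bound is a mathematical limit. Correlations declining with time usually give milder values; an autoregressive pattern with ρ = .6, for example, gives 0.90.
- **Other analyses.** The mixed model and the one-degree-of-freedom contrast in Data analysis do not use this ε correction, and Sample size offers the ANOVA only as an example of the planned analysis.

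None of this makes the sentence true. Under the method and inputs the section reports, ε = 1 is the least conservative choice.

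**Conclusion.** The statement about ε is wrong as written: it is the most favourable value, and 74 is the minimum N under sphericity. By the protocol's own method, 74 analysed GPs have essentially no tolerance (below .80 once ε is under about 0.98, and .597 at the 0.5 bound). One hundred analysed GPs have considerable tolerance (.80 down to about 0.635, and .730 at the bound).

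This rests on f = 0.15, r = .50, α = .05 and G*Power's ε scaling for the omnibus interaction test. It does not show that the trial is underpowered. ε is unknown before data, the simulated results go both ways, and the other planned analyses are not governed by this correction. It is a correction to the sample-size rationale; it does not call for a change in design or target.

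**What to change.** In Sample size:
1. Replace the clause that calls ε = 1 the conservative case with a statement that it is the most favourable assumption.
2. Describe 74 as the minimum required under sphericity.
3. Report power for N = 74 and N = 100 at ε = 0.5, 0.75 and 1: .597, .719 and .806 for 74; .730, .846 and .914 for 100. Note that the figures for 100 assume no loss and that all of them apply to the omnibus ANOVA under G*Power's approximation.

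A power statement for the single contrast already planned could be added, since it avoids the sphericity assumption, but this is optional.

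The cost is a wording change, a small table and a less favourable stated power. No extra participants and no change to the analyses are needed.
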